### Study eligibility

#### Inclusion criteria

Age 65 and older, a valid driver’s license, evidence of insurance, use of a passenger car or pickup truck, age and education-adjusted Montreal Cognitive Assessment (MoCA) [17] score of 19 or higher, and a willingness to return to one of three testing/installation sites for retesting, data download, and sensor maintenance as needed every 3 months, are all requirements for inclusion. Potential participants must also be able to speak English, Spanish, or Haitian Creole and pass the standard state driver’s license requirements for vision, hearing, strength, and flexibility.

#### Exclusion criteria

Those who are under 65, do not have a vehicle to drive, a valid driver’s license or insurance, score below 19 on the MoCA [17], cannot return every 3 months for retesting and sensor maintenance, cannot pass the physical screening, or decline to sign the Institutional Review Board-approved written consent, or are not fluent in either Spanish, English or Creole, will be excluded. We will exclude those with a clinically significant active illness, neurological or psychiatric disorders, or loss of consciousness within the last 5 years and those who cannot meet the state physical ability requirements for vision or hearing.

### Participant recruitment

A community outreach approach to participant recruitment will be led by a dedicated study recruiter with prior research experience. The recruitment effort will begin with networking with representatives of community-based senior services, either at networking events or in individual meetings. This high-level networking is directed to developing connections with organizations that serve the age 55+ segment of the population to elicit invitations to conduct formal and informal information sessions with the older clients/members/residents in their communities, programs, and services. This includes senior living communities, senior day programs, places of worship, and, secondarily, health services. Presentations and discussions with potential participants will be done in English, Spanish, and Haitian Creole. Bilingual research team members will join the study recruiter to conduct the meetings with primarily non-English speaking groups. Printed materials about the study will be available in these languages, as well as information on how to connect with the study team to enroll. Another smaller recruiting effort will be primarily participant-driven. With Institutional Review Board approval, participants who introduce an eligible individual to the study are given an additional gift card for each new enrollee referred.

Individuals who express interest in participation receive further explanation of the study and what participation entails. They are then briefly screened for eligibility, and an appointment is made. On the first visit, further explanation of the study is provided, consent is obtained, eligibility is confirmed, and baseline tests are administered. A sensor installation team places the telematic and video sensors in the participants’ vehicle once consent is obtained and eligibility confirmed.

### Sensor instrumentation

The in-vehicle sensor network uses open-source hardware and software components to reduce the time, risks, and costs associated with developing in-vehicle sensing units. In-vehicle sensor systems are kept simple and compact by minimizing complex wiring, limiting the size of the sensing units, and limiting the number of sensors in a vehicle to support the unobtrusiveness of in-vehicle sensors. Each in-vehicle sensor system is comprised of two distributed sensing units: one for telematics data and the other for video data.

#### Telematic units

The telematics unit of the in-vehicle sensor system is built upon Raspberry Pi which enables the modification and adaptation of telematics sensor data types, sampling frequencies, and onboard data logging algorithms. A vehicle’s On-Board Diagnostic (OBD) port provides 12-V power to a telematics unit. Furthermore, the telematics unit has a smart power control system based on the voltage of an OBD port to prevent battery drainage. The telematics unit uses ten mA (milliamps) up to 500 mA when a vehicle is in use or not in use, respectively. The processor of the telematics units has a heat sink to provide stable and reliable operations in Florida’s hot climate.

The telematics sensor provides three data types: Inertial measurement unit (IMU), OBD, and GPS data. IMU data comprise 3-axial acceleration and 3-axial gyroscope (e.g., angular velocity) to capture vehicles’ dynamic motions and orientations. IMU data will be processed to determine hard braking, hard accelerations and hard turns, and GPS data. It also includes a timestamp, latitude, longitude, altitude, course over ground (COG), and the number of communicating satellites. The first four will constitute the trajectory of a vehicle and be used to analyze travel patterns (e.g., travel distance, trip purpose). COG data will be used to calculate the heading information of a vehicle. The number of satellites connected to GPS sensors will be used to analyze the accuracy of GPS information. A minimum of four satellites provides the roughest estimation of location, while 7 to 8 satellites are needed to estimate an accurate location within 10–11 yards [18]. The sampling rates of the IMU sensor, gyroscope, and GPS data are set to 12.5 Hz, 25 Hz, and 1 Hz, respectively.

The telematics sensor employs hybrid data logging systems: onboard and cloud data logging. High-resolution telematics data will be stored in local (in vehicle) data stores, manually collected and uploaded to a secure central database during participants’ quarterly visits. The in-vehicle sensor has cellular connectivity. The Cloud database will be used primarily to check the operating state of in-vehicle sensors (e.g., error messages, local data connectivity, operating condition of camera units through Wi-Fi connections), software updates through 4G connections (e.g., change sampling rates, update OBD parameters, firmware update), and troubleshoot malfunctioning devices (e.g., remote control through 4G connections). See Fig. 1.

**Fig. 1 Fig1:**
[figure not shown]
The architecture of telematic units

#### Video unit

The video unit consists of the MDVR (Digital Video Recorder), a driver-facing camera, and a forward-facing camera (see Fig. 2). The MDVR has a storage unit with a capacity of 256 GB, which allows storing the video from both cameras for a period of 3 months. The MDVR has built-in AI functions that analyze video in real-time. The driver-facing camera is mounted in the left corner of the windshield and is directed to the driver’s face to analyze his/her behavior and facial expressions. Table 1 shows a list of indices that are analyzed by the driver- facing camera.

**Fig. 2 Fig2:**
[figure not shown]
**A** Installation of AI (Artificial intelligence)-embedded cameras. The Advanced Driver Assistance System (ADAS) camera faces outwards and is located at the top center of the windshield. The Driver Monitoring System (DMS) faces the participant driver and is located at the bottom left of the windshield. **B** Close-up of the Artificial Intelligence Module Digital Video Recorder (MDVR). **C** The ADAS and the DMS

**Table 1 Tab1:** Driver-facing camera indices

Behavior Indices	Description
Face detection	AI algorithm detects the face of the driver and the driver’s features.
Eye detection	AI algorithm detects the eyes and whether they are open or closed.
Yawning	Using eye and mouth detection, yawning is detected.
Distraction	Head-pose estimation technique is applied to detect distraction.
Smoking Mobile Phone Use	Driver’s smoking and use of mobile phones are detected using an AI algorithm.

The forward-facing camera is mounted under the rear-view mirror and is used to record events external to the vehicle. Table 2 shows the list of indices that are recorded and analyzed using the front-facing camera.

**Table 2 Tab2:** Forward-facing camera indices

Behavior Indices	Description
Traffic Sign Detection	AI algorithm detects traffic signals and monitors if the driver runs a red traffic light.
Object Detection	AI algorithm detects objects on the road, such as pedestrians or cyclists crossing the road, curbs or barriers, and nearby vehicles.
Lane Crossing	AI algorithm detects lane departure.
Near-Collision	AI algorithm can detect an object or a vehicle that is close to the driver’s car.
Pedestrian Detection	AI algorithm detects whether the driver yields when a pedestrian crosses the street.

### Cognitive battery

#### Measure selection

The team assembled the neuropsychological assessment protocol with two aims: 1. To classify participants into three diagnostic groups: mild cognitive impairment (MCI), early dementia, and unimpaired (normal). 2. To detect subtle changes over time in these measures independent of clinical assessments, particularly in executive function and visual attention, which are the cognitive domains most strongly associated with driving variables.

To fulfill these aims, two groups of tests were assembled: A clinical battery including assessments of cognition, functioning in daily activities, and mood (depression), and an additional set of tests including executive function and attention.

### Clinical battery

#### Global cognitive function

*The Montreal Cognitive Assessment (MoCA)*, is a measure of global cognitive function [17] originally developed to detect mild cognitive impairment (MCI) and now frequently used as a screening test. It is a 10-min test that assesses short-term memory, visuospatial function, executive function, attention, concentration, working memory, language, and orientation.

#### Executive function

*Trail Making Test* [19–21] is predominantly a measure of divided attention and two components of executive function, cognitive response set maintenance and shifting. The primary outcome measure for each TMT is time in seconds. Additionally, a derived Trails B/Trails A ratio will be calculated to obtain a relatively independent measure of executive control [22].

*The Stroop-Color Word Test (SCWT)* is a neuropsychological test used in both clinical and experimental settings [23]. This test measures the ability to inhibit cognitive interference that may occur while processing two stimuli simultaneously. The processing of one stimulus (e.g. color) may interfere with the second stimulus (e.g. word) processing, causing a Stroop Effect, in which the participant may confuse one stimulus for the other. Participants will be tested for color blindness prior to administration of this test.

#### Semantic memory

##### Loewenstein-Acevedo Scales of Semantic Interference and Learning (LASSI-L)

Participants are tasked with remembering two lists with 15 words each including fruits, musical instruments, or clothing. The words are presented one at a time on cards and are read by the participant. Participants are made aware of the semantic categories. This is followed by a free recall trial and then cued recall trials for each of the 3 categories. List A is presented again, and an additional cued recall trial for each category is conducted. A second list (List B) is subsequently presented, followed by a free recall trial, then three cued recall trials (one per category). List B is presented for a second time, with another round of cued recall trials. Then the participant is asked to think back to List A followed by the free recall and cued recall trials of List A. Participants are allowed 60 s during free recall trials and 20 s for each semantic category during cued recall trials. After 20 min, there is a delayed free recall of both lists. Previous analyses of the LASSI-L have demonstrated its sensitivity in differentiating between MCI and cognitively normal participants [24]. Semantic interference tasks similar to the LASSI-L have been shown to be valid across participants with different cultural backgrounds [25].

##### Logical memory

The Craft Story is a logical memory test that typically takes 20 min to administer [26]. The examiner reads a short story of approximately 60 words aloud and then asks the individual to recall as much detail as possible both immediately and after a 20-min delay.

#### Visuospatial and visuomotor

*The Benson Figure Drawing (BFD)* [27] has been used to evaluate visuospatial cognition in dementia. The patient is asked to copy a figure with no limit on response time.

#### Language

##### Naming

The Multilingual Naming Test (MINT) assesses confrontation naming with 32 pictures of objects [28]. It detects naming deficits in patients with MCI or AD [29].

*Verbal Fluency (VF)* will be assessed using category (animals) [30] and phonemic (letters P and F) fluency [31]. Successful performance on word fluency tasks requires executive functions such as inhibiting words that do not conform to the rules of the task. Although often conceptualized as measuring executive functioning, recent analyses showed that language processing is the critical component [32].

#### Functional ability measures

*The Functional Activities Questionnaire (FAQ)* measures instrumental activities of daily living (IADLs) affected by changes in cognition, such as preparing balanced meals and managing personal finances [33, 34].

*Everyday Cognition (ECog)* [35] consists of one global everyday function scale and six subscales (Everyday Memory, Language, Visuospatial Abilities, Planning, Organization, and Divided Attention). The ECog has shown sensitivity to MCI [35, 36].

#### Mood

The Geriatric Depression Scale-Short form (GDS-15) [37, 38] will be used to measure the level of depression symptom severity.

#### Clinical rating

*The Clinical Dementia Rating Scale (CDRS)* [39] is a 5-point scale used to quantify the severity of cognitive impairment symptoms. Six domains of cognitive performance are measured: Memory, Orientation, Judgement and Problem-solving, Community Affairs, Home and Hobbies, and Personal Care. These domains are relevant to the diagnosis and severity of Alzheimer’s Disease and Dementia. The CDRS score is derived from information collected from an informant (study partner) interview as well as a participant interview.

### Additional measures

#### Executive function

##### ***Cogstate: Identification (IDN) task***

The Identification (IDN) [40] task is a simple choice reaction time paradigm that measures reaction time and decision-making.

##### ***Arrow Flanker Task (AFT)***

The Flanker Task [41, 42] is a neuropsychological task that measures inhibition using non-verbal stimuli such as arrows. It assesses the ability to suppress unrelated responses.

##### **Cogstate: One Back (ONB) and Two Back (TWOB) task**

These two tasks [40] assess working memory and attention.

*Cogstate: The Groton Maze Learning Test (GMLT)* [40] is designed to measure executive function using a maze learning paradigm.

#### Visual attention

*The Useful Field of View test (UFOV)* is a measure of three perceptual-cognitive abilities: processing speed, divided attention, and selective attention. These three tasks represent higher-order cognitive functioning required for safe vehicle driving [43]. The UFOV software (version 6.1.4; Visual Awareness Research Group Inc.) will be used.

### Clinical diagnosis

A clinical diagnosis will be made using an algorithm that has demonstrated reliability and validity in the diagnosis of MCI and dementia [44]. It combines the CDR clinical ratings with the neuropsychological test-based diagnosis (see Table 3). Cases in which there is a disagreement between the clinical ratings and test results will be presented to an expert panel of 4 clinical experts (2 neuropsychologists, a neurologist, and a geriatric nursing specialist) at a consensus diagnostic panel meeting.

**Table 3 Tab3:** Algorithmic diagnosis including Clinical Dementia Rating (CDR) scores and neuropsychological test-based diagnosis of normal, amnestic and non-amnestic Mild Cognitive Impairment (aMCI; naMCI) and early (eMCI) and late MCI (LMCI)

CDR Sum of Boxes	Neuropsychological Diagnosis (NpDx)			
	Normal	aMCI	naMCI	Dementia
0	Normal	PreMCI –NP	PreMCI-NP	Consensus Conference
0.5–2.0	PreMCI Clinical	eMCI	eMCI	Consensus Conference
2.5–4.0	PreMCI Clinical	eMCI	eMCI	LMCI
4.5+	Consensus Conference	Dementia	Dementia	Dementia

[Rule 1: CDR-sb score > 4.0 indicates dementia diagnosis (except when NpDx is Normal)]

[Rule 2: CDR-sb score of 2.5 to 4.0 indicates an LMCI diagnosis (except when NpDx is Normal)]

[Rule 3: CDR-sb score of 0.5 to 2.0 indicates an eMCI diagnosis (except when NpDx is Normal)]

[Rule 4: Pre-MCI is diagnosed when CDR-sb 0.5–4.0 and NpDx is normal, or CDR-sb = 0 and NpDx = aMCI or naMCI]

*CDR-sb* = CDR sum of boxes, *aMCI* = Amnestic MCI, *naMCI* = Non-amnestic MCI, *LMCI* = Late MCI, *eMCI* = Early MCI

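### Table 3 and its Rule 2 give different MCI stages (eMCI against LMCI) in two cells, and Rule 3 omits a consensus referral that the table makes

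*Protocol article*

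**What the plan says.** The Clinical diagnosis section says that diagnosis follows a published algorithm combining CDR ratings with a test-based diagnosis (NpDx), and that cases where the two disagree go to a four-member expert panel. Table 3 then sets out four CDR-sb bands by four NpDx categories (Normal, aMCI, naMCI, Dementia). Its title names early and late MCI among the outputs.

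The two grid rows that matter are:
- "2.5–4.0 PreMCI Clinical eMCI eMCI LMCI"
- "0.5–2.0 PreMCI Clinical eMCI eMCI Consensus Conference"

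The rules for the same two bands are printed under the table. Rule 2 covers the upper band and allows a single exception: "CDR-sb score of 2.5 to 4.0 indicates an LMCI diagnosis (except when NpDx is Normal". The lower band is the subject of Rule 3, which is worded in parallel and allows the same single exception: "CDR-sb score of 0.5 to 2.0 indicates an eMCI diagnosis (except when NpDx is Normal".

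Nothing states whether the grid or the rules take precedence. The section on preparation of assessors and psychometricians makes this procedure the one that the diagnosing team uses. The Aims section lists diagnostic groupings as one of three kinds of change that the sensors are tested against, beside individual measures and latent constructs.

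**The concern.** A participant with an MCI-level NpDx and a CDR-sb of 2.5–4.0 is staged eMCI by someone who reads the grid and LMCI by someone who reads the rules. The grid gives LMCI in only one cell, the one with a Dementia-level NpDx, so it makes no early/late distinction at all within aMCI or naMCI.

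In a study of change over three years this affects which transitions are recorded. If NpDx stays at aMCI or naMCI while CDR-sb rises from 0.5–2.0 to 2.5–4.0, the grid records no change and Rule 2 records a move from eMCI to LMCI. Any label of diagnostic change that uses the MCI substage would inherit that ambiguity. Participants are tested at more than one institution (Testing locations), so the text should allow only one reading.

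**Working it through.** No sample size or error rate is involved. The check applies Rules 1–4 to each of the 16 grid cells and compares the result with the printed entry.

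Inputs, all from Table 3 and the notes beneath it, are the two rows and two rules quoted above, together with:
- row 0: Normal, PreMCI, PreMCI, Consensus Conference;
- the top row: "4.5+ Consensus Conference Dementia Dementia Dementia";
- Rule 1, which gives dementia for any score above 4.0 unless the NpDx is Normal;
- Rule 4, which gives Pre-MCI in two situations: a Normal NpDx at a score of 0.5–4.0, and an aMCI or naMCI NpDx at a score of 0.

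Rule 1's threshold (above 4.0) is taken as the grid's 4.5+ row. The two PreMCI subtypes in the grid are both counted as the Pre-MCI of Rule 4.

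| CDR-sb | NpDx | Grid | Rule result | Comparison |
|---|---|---|---|---|
| 0 | Normal | Normal | none applies | – |
| 0 | aMCI | PreMCI | R4: PreMCI | agree |
| 0 | naMCI | PreMCI | R4: PreMCI | agree |
| 0 | Dementia | Consensus | none applies | – |
| 0.5–2.0 | Normal | PreMCI | R4: PreMCI | agree |
| 0.5–2.0 | aMCI | eMCI | R3: eMCI | agree |
| 0.5–2.0 | naMCI | eMCI | R3: eMCI | agree |
| 0.5–2.0 | Dementia | Consensus | R3: eMCI | **referral against diagnosis** |
| 2.5–4.0 | Normal | PreMCI | R4: PreMCI | agree |
| 2.5–4.0 | aMCI | eMCI | R2: LMCI | **different diagnosis** |
| 2.5–4.0 | naMCI | eMCI | R2: LMCI | **different diagnosis** |
| 2.5–4.0 | Dementia | LMCI | R2: LMCI | agree |
| 4.5+ | Normal | Consensus | none applies | – |
| 4.5+ | aMCI | Dementia | R1: Dementia | agree |
| 4.5+ | naMCI | Dementia | R1: Dementia | agree |
| 4.5+ | Dementia | Dementia | R1: Dementia | agree |

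Cells covered by a rule: 3 (R1) + 3 (R2) + 3 (R3) + 4 (R4) = 13. Agreeing: 3 + 1 + 2 + 4 = 10. Not agreeing: 13 − 10 = 3, of which 2 are different diagnoses and 1 is a referral against a diagnosis. Not covered by any rule: 16 − 13 = 3; these are not conflicts.

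Effect on recorded transitions:
- NpDx fixed at aMCI or naMCI, CDR-sb moving from 0.5–2.0 to 2.5–4.0: the grid gives eMCI to eMCI (no change); the rules give eMCI to LMCI (change).
- CDR-sb fixed at 2.5–4.0, NpDx moving from aMCI or naMCI to Dementia: the grid gives eMCI to LMCI (change); the rules give LMCI to LMCI (no change).

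So the two versions do not merely differ in sensitivity. They count different events.

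Effect on the broad grouping: eMCI and LMCI are both MCI, so the three groups named under Measure selection (MCI, early dementia, unimpaired) are the same under either version in the two Rule 2 cells.

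**The case against.** The strongest objections concern consequence rather than fact.

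- **The third cell is not a second diagnosis.** The body text sends disagreements between ratings and tests to the panel, and a Dementia NpDx with a CDR-sb of 0.5–2.0 is plausibly such a case. This stands. Grid and body text agree, and the fault is an exception missing from Rule 3. A reader might infer that three cells give contradictory diagnoses, or that cases will bypass the panel. The latter would require applying Rule 3 while ignoring both the grid and the paragraph above it.
- **Diagnosis is not the only target.** Aims lists three kinds of change and illustrates groupings by a move from unimpaired to MCI. Measure selection also seeks subtle change in the tests apart from clinical assessment. The predictive modeling section speaks of overall cognition and specific domains, and the sample size rests on Change against No-Change in cognition. No section names an eMCI-to-LMCI transition as an endpoint. This stands, and it rules out calling this diagnosis the one outcome on which the sensor models are trained.
- **The panel resolves the matter.** This fails for the two Rule 2 cells, because the grid assigns them a diagnosis without referral.
- **The table may have been damaged in extraction.** It shows four complete rows of four entries, and Rules 1 and 4 match it wherever they apply, so shifted columns are not evident.
- **Clinicians make the diagnosis, not a program.** That is so, but they do it with this algorithm, and the text gives them two answers.

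**Conclusion.** The contradiction is real and confined. Two of 16 cells (CDR-sb 2.5–4.0 with aMCI or naMCI) carry two different diagnoses, and one further cell (0.5–2.0 with Dementia) shows a consensus referral that Rule 3 does not list. Early/late MCI staging, and any change label that uses it, depends on which version is applied.

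A reader might conclude that the study's main diagnostic classification is compromised. The documents do not support that: the two conflicting cells leave the unimpaired/MCI/dementia grouping unchanged. Only the third cell could move someone between broad groups, and only if Rule 3 were followed literally and the panel would have decided otherwise.

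The size in participants is unknown, because the article gives no expected number in these cells. The conclusion assumes that table and rules are reproduced as published. It does not show that the source algorithm is faulty, and the documents do not show which version is intended. It still needs correcting, because this is the operative diagnostic rule and not background text.

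**What to change.** The clinical leads should compare the grid and Rules 2 and 3 with the cited source algorithm and confirm the intended entry for the two cells at CDR-sb 2.5–4.0. One version should then be printed and applied at all sites. Rule 3 should be made consistent with the consensus referral in the grid and body text. Any diagnoses already made in the three cells should be re-checked against the confirmed version before they are used as labels, and the protocol should say whether a change of MCI substage counts as a change in diagnostic grouping.

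The cost is a short correction to the table or rule text and a look-up of any affected visits from CDR-sb and NpDx values. It needs no new data and no change to the sample size.
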